## Abstract

**Background:**

The increased prevalence of autism spectrum disorder creates a sense of urgency to improve outcomes for this population in publicly funded education systems, the primary setting in which autistic children receive behavioral health services in the United States. Important barriers to progress include a lack of feasible clinical interventions that address autistic children’s externalizing behaviors in schools and major challenges sustaining fidelity to newly implemented programs over time. This trial addresses these gaps by (1) testing the clinical effectiveness of the Research Units on Behavioral Interventions in Educational Settings (RUBIES) program relative to educator psychoeducation on externalizing behaviors of autistic children in public elementary schools, and (2) testing the effects of adding a leadership-focused organizational implementation strategy, Helping Educational Leaders Mobilize Evidence (HELM), to educator coaching in RUBIES on RUBIES sustainment.

**Methods:**

In a cluster-randomized, hybrid type 2 effectiveness-implementation trial, schools will be randomized to one of 3 arms: 1) educator coaching in RUBIES and school participation in HELM; 2) educator coaching in RUBIES only; or 3) a control condition incorporating an active clinical comparator, educator psychoeducation. We will enroll 42 schools and 126 educators yoked to 126 elementary-aged autistic children. Depending on arm, educators will complete study instruments up to six times: 1) Spring semester prior to the year of school and student enrollment (implementation baseline; arms 1–2); 2) Fall semester Year 1 (clinical baseline; arms 1–3); 3) 16 weeks (arms 1–3); 4) 24 weeks (arms 1–3); 5) 52 weeks (arms 1–2); and 6) 76 weeks (arms 1–2). The primary clinical outcome compares arms 1 & 2 vs. 3 on change in autistic children’s externalizing behavior from clinical baseline to 24 weeks. The primary implementation outcome compares arms 1 vs. 2 on RUBIES sustainment, operationalized as educators’ average RUBIES fidelity at 52 and 76 weeks.

**Discussion:**

Generating evidence for the clinical effectiveness of RUBIES addresses a significant gap in educator-delivered interventions to minimize highly prevalent externalizing behaviors among autistic children in public schools. Simultaneously, testing the effectiveness of HELM on sustainment of RUBIES will inform future efforts to successfully implement and sustain new innovations for autistic youth in public schools.

**Name of the registry:**

Clinical Trials.

**Trial registration:**

NCT07276750.

**Date of registration
**

12/10/25.

**URL of trial registry record**

https://clinicaltrials.gov/study/NCT07276750?cond=Autism&intr=RUBIES&rank=1.

Contributions to the literature
Sustainment of evidence-based practices in schools is challenging given the implementation cliff that occurs oversummer break in-between school years. This study will simultaneously evaluate the clinicaleffectiveness of a promising, relatively low-cost, and highly feasible intervention that addressesexternalizing behavior in autistic students, called RUBI in Educational Settings (RUBIES), and theimplementation effectiveness of a promising leadership-focused implementation strategy calledHelping Educational Leaders Mobilize evidence (HELM), in public elementary schools.The proposed trial will generate evidence regarding the clinical effectiveness of RUBIES which fills agap in educator-delivered interventions that meaningfully support autistic youth throughout theschool day to minimize externalizing behaviors.Leadership-focused implementation strategies have shown promise for improving fidelity in othersettings; however, their effects on sustainment and in public schools remains unexamined. Theproposed trial tests whether the addition of HELM improves sustainment of evidence-based practicesin public elementary schools beyond educator coaching alone.If successful, this study will have substantial public health impact because it will produce an effectiveintervention for a prevalent problem among a high impact population and will determine how tosustain this (and other) intervention(s) with high fidelity.

## Background

Autism is a complex and lifelong developmental disorder that affects 1 in 31 children in the United States [1, 2]. The high and increasing prevalence of autism places a significant obligation on public education systems [3, 4]. For example, in the U.S., public schools are the primary setting in which autistic children receive behavioral health interventions, partly due to federal laws (e.g., Individuals with Disabilities Education Act) that require supports for children with disabilities [3, 4]. However, most educators receive limited training, resources, and support for working with autistic students, contributing to poorer academic, behavioral, and social outcomes for autistic children [5].

Autistic children commonly exhibit externalizing behavior (e.g. physical/verbal aggression, property destruction, transition difficulties) in schools, which significantly hampers their participation in less restrictive environments [6–10]. Externalizing behavior persists if unaddressed, and is a major contributor to educator burnout and turnover [11, 12]. Moreover, these challenges have additive short-term (e.g. increased rates of physical restraint, seclusion, suspension, expulsion) and long-term impacts (e.g. dropout, trauma, exacerbated mental health issues) [10, 13, 14]. Therefore, there is a critical need to increase the feasibility, efficiency, and effectiveness with which autistic children’s externalizing behaviors are addressed in classrooms.

There are currently no widely disseminated evidence-based interventions for educators to effectively and efficiently address externalizing behavior of autistic children in schools. The Research Units on Behavioral Interventions in Educational Settings (RUBIES) intervention is a promising intervention designed to help educators functionally evaluate and understand autistic children’s externalizing behavior as communication, and to account for autistic characteristics (e.g. rigidities and sensory sensitivities) in responding to that behavior [15]. RUBIES was adapted from RUBI, an empirically-validated caregiver-mediated behavioral intervention for autistic children with co-occurring externalizing behaviors [16, 17]. The adapted RUBIES intervention includes 9 modules and provides a simple framework that helps teach educators how to identify the function of a child’s behavior in order to apply a tailored positive behavioral support strategy that addresses the behavior’s function [18–20]. Previous studies indicate RUBIES is feasible, acceptable, and appropriate for schools; however, its clinical effectiveness in reducing child externalizing behaviors in schools has yet to be evaluated [21].

Clinical interventions such as RUBIES cannot meaningfully improve population health if they are not implemented with fidelity (i.e., the extent to which the intervention is implemented as designed) and sustained (i.e., the degree to which the intervention continues to be delivered with fidelity in a setting) over time [22, 23]. Malleable organization-level factors, including leadership, culture and climate, and operating policies and procedures, frequently stymie efforts to implement autism interventions with fidelity in schools and sustain them over time [24–26]. Previous research has highlighted two related malleable organizational factors that are particularly effective in predicting evidence-based practice (EBP) fidelity: implementation leadership (i.e., specific leader behaviors that support EBP use) and implementation climate (i.e., shared perceptions among intervention users of the extent to which EBP use with fidelity is expected, supported, and rewarded within the setting) [24, 27–29]. Research indicates that implementation strategies targeting implementation leadership and climate can improve fidelity to and the effectiveness of clinical interventions, as well as create an environment that is conducive to EBP sustainment over time [30–32].

Although organizationally focused implementation strategies have shown promise, schools represent a unique context, requiring adaptations to the form of organizational strategies as well as unique tests to confirm these strategies are effective within school settings. For example, the perpetual shifts in staff, students, operating policies and procedures, and emergent crises that plague public schools require specific modification to support high-fidelity EBP use to achieve positive outcomes for students [33]. To address this gap, we used the Discover, Design/Build, and Test framework [34] to collaboratively redesign, with school leaders and staff, one of the most promising organizational implementation strategies called Leadership and Organizational Change for Implementation (LOCI). The LOCI strategy targets general and implementation-specific leadership to improve implementation climate for a specific EBP [35]. LOCI includes a) data-based feedback; b) coaching of first-level leaders to enhance transformational and implementation leadership, and c) strategy meetings with executive leaders to improve implementation climate [36, 37]. Studies show that LOCI improves implementation leadership and climate, as well as EBP fidelity in mental health and substance abuse settings; however, this strategy has not previously been systematically adapted to improve EBP sustainment in school settings [35, 38].

Our collaboratively redesigned, school-focused organizational implementation strategy was called HELM for Helping Educational Leaders Mobilize evidence. HELM works with school building leadership teams (including the school principal and assistant principal) to improve the team’s implementation leadership and ability to develop a supportive implementation climate, with the ultimate goal of supporting EBP fidelity and sustainment within the school context. Results from a pilot study evaluating HELM indicated it was feasible and acceptable to school principals and staff and significantly improved implementation leadership and climate compared to an implementation attention control condition [39]. However, the effects of HELM on EBP fidelity and sustainment have not yet been tested.

## Study purpose and aims

The purpose of this study is to test both RUBIES and HELM in a large-scale cluster-randomized, hybrid type 2 effectiveness-implementation trial and to evaluate the mechanisms through which these interventions influence their targeted outcomes [40]. In the trial, schools will be randomized to: Arm 1) educator coaching in RUBIES and school leadership participation in HELM; Arm 2) educator coaching in RUBIES only; or Arm 3) an active clinical comparator, educator psychoeducation. The primary clinical comparison contrasts arms 1 and 2 versus arm 3 on improvement in autistic youths’ externalizing behavior. The primary implementation comparison contrasts arms 1 versus 2 on RUBIES sustainment. If successful, this study will identify an effective clinical intervention for reducing externalizing behavior of autistic children in schools (RUBIES) and an organizational implementation strategy specifically designed to sustain RUBIES and other EBPs in schools with high fidelity (HELM). Because HELM can be applied to a range of EBPs, results are expected to generalize with strong potential for scale up and public health impact.

Figures 1 and 2 depicts core HELM and RUBIES components, their respective mechanisms of change, and targeted outcomes. Evaluation of implementation mechanisms is critical to developing effective and streamlined implementation strategies [41, 42]. In our conceptual model, we theorize that RUBIES will activate the *child-level mechanism* of self-management skills which will impact the clinical outcome of externalizing behavior. We also theorize that HELM will activate *organizational mechanisms* of implementation leadership and climate which will impact the implementation outcome of sustainment.

**Fig. 1 Fig1:**
[figure not shown]
RUBIES components, hypothesized mechanisms, and target outcomes

**Fig. 2 Fig2:**
[figure not shown]
HELM components, hypothesized mechanisms, and target outcomes

The trial tests the following hypotheses:

### Hypothesis 1

During Year 1 of school enrollment, RUBIES will significantly reduce autistic children’s externalizing behavior from clinical baseline to 24 weeks compared to educator psychoeducation (arms 1 & 2 vs. arm 3).

### Hypothesis 2

During Year 2 of school enrollment, educator sustainment of RUBIES (operationalized as level of educator fidelity to RUBIES through the second year of study enrollment) will be superior in schools that receive HELM relative to schools that do not receive HELM, 52 and 76 weeks after clinical baseline (arm 1 vs. arm 2).

### Hypothesis 3a

Increases in autistic children’s self-management skills will mediate RUBIES’ effect on autistic children’s externalizing behavior relative to educator psychoeducation (arms 1 & 2 vs. arm 3).

### Hypothesis 3b

Increases in principal implementation leadership and school implementation climate will mediate HELM’s effect on educator sustainment relative to RUBIES coaching alone (arm 1 vs. arm 2).

## Method

### Study design

This study will use a hybrid type 2 effectiveness-implementation trial with HELM, RUBIES, and a psychoeducation only control condition to provide a rigorous test of the effects of RUBIES and HELM across 126 educators paired with 126 autistic children in 42 elementary schools. The full sample of 42 elementary schools will be enrolled in three cohorts of approximately 14 schools each nationwide. Each cohort will participate for two years. Depending on arm, educators will complete study instruments up to six times: 1) Spring semester prior to the year of school and student enrollment (implementation baseline; arms 1–2); 2) Fall semester Year 1 (clinical baseline; arms 1–3); 3) 16 weeks (arms 1–3); 4) 24 weeks (arms 1–3); 5) 52 weeks (arms 1–2); and 6) 76 weeks (arms 1–2). Leaders and educators will be compensated $40 at implementation and clinical baseline, $50 at Week 16, $60 at Week 24, $70 at Week 52, and $80 at Week 76 for the completion of study instruments at each timepoint. See Fig. 3 for study design.

**Fig. 3 Fig3:**
[figure not shown]
Study design illustrated with cohort 1

### Randomization

The biostatistician (WS) will generate the random allocation sequence; all other research team members will not have access to the randomization sequence. Schools in each cohort will be randomized (1:1:1) to one of three parallel arms (*n* = 14 schools per arm): 1) RUBIES + HELM; 2) RUBIES only; 3) or educator psychoeducation. Randomization will be stratified based on median split for: 1) size of school at the time of enrollment; and 2) number of possible dyads (identified at screening for each enrollment cohort). Study enrollment, randomization, and engagement for all schools begins in the Spring prior to Year 1. Schools randomized to psychoeducation will be enrolled in the trial for one year; schools randomized to either RUBIES + HELM or RUBIES only will be enrolled in the trial for two years; children will be enrolled for one year.

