### Autistic children

Enrolled educators will identify one autistic child with whom they currently work for potential enrollment in the trial. Educators will share information about the study with the child’s caregiver/legal guardian and ask to share the caregiver’s contact information with the research team to complete informed consent. Consenting caregivers will be contacted by the research team. All study activities will be described verbally and in writing during the caregiver informed consent process. The research staff will describe the study and expected roles and responsibilities, risks and benefits, and confidentiality procedures and will obtain electronic parent/guardian consent. Autistic children enrolled in the trial will be paired with one educator (1:1 dyad). We anticipate recruiting at least two autistic children per school (range 2–5 children per school). Inclusion criteria for children are: 1) a documented autism diagnosis via school records (i.e., Individualized Education Program; IEP); 2) enrolled with a participating educator; 3) in grades K-5; ages 5–12; and 4) a Sutter Eyberg Student Behavior Inventory-Revised (SESBI-R) [43] total score ≥ 101 and/or an Emotion Dysregulation Inventory [44] sum score of ≥ 8 at baseline as rated by the educator after the dyad consents. Educators will be excluded if their principal/administrator declines participation. If an educator serves no autistic children who meet eligibility criteria, the educator will be excluded.

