### Sample size and power

The primary focus of Aim 1 is to test the main effect of RUBIES (RUBIES + HELM and RUBIES only) vs. educator psychoeducation on change in children’s externalizing behavior from Baseline to Week 24. Assuming a Type-I error rate of 5% and SD of 6.2, a conservative within-person correlation in externalizing behavior of r = 0.3, 10% intraclass correlation (clustering within schools) for variance inflation and 20% attrition rate in children, a total of 126 autistic children paired 1:1 with educators (84 autistic children for RUBIES + HELM and RUBIES only vs. 42 children in educator psychoeducation) nested within 42 schools are needed to detect a difference of at least 3.8 points in the comparison of slopes in ABC-I with 80% power. A difference of 3.8 corresponds to a moderate standardized effect size of d = 0.62 in between groups change in children’s externalizing behavior and this effect size is clinically meaningful based on prior research [16]. The study assumed a modest clustering within schools of 10% because of the 1:1 pairing of the educator and autistic child. We expect 3 child-educator dyads per school to consent and enroll in the study. Hence, a total of 126/3 = 42 schools are needed.

For Aim 2, we will use only educators in the RUBIES + HELM vs. RUBIES only (84 educators within 28 schools) arms. With 84 educators as the effective sample size (42 each), nested within 28 schools, we have 80% power to detect a difference of at least 0.13 (or d = 0.76) in RUBIES sustainment (Week 52 and Week 76) between RUBIES + HELM vs. RUBIES only assuming SD = 0.17 based on pilot RUBIES data, a Type-I error rate of 0.05, 10% variance inflation for clustering within school effect, 25% attrition rate and within-person correlation of observations = 0.3. We assumed a higher attrition rate for educators since the turnover rate for educators are higher post pandemic.

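### Four strata in cohorts of about 14 schools give three arms only partial balance, and the models as described omit the stratification factors and cohort

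*Protocol article*

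**What the plan says.** Study design: "The full sample of 42 elementary schools will be enrolled in three cohorts of approximately 14 schools each nationwide".

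Randomization: "Schools in each cohort will be randomized (1:1:1) to one of three parallel arms", with 14 schools per arm as the stated total. On the strata: "Randomization will be stratified based on median split for: 1) size of school at the time of enrollment; and 2) number of possible dyads". The dyad count is "identified at screening for each enrollment cohort". On the sequence, the article says that the biostatistician "will generate the random allocation sequence; all other research team members will not have access to the randomization sequence". It gives no block size, no rule on whether lists restart, and no other allocation method.

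Sample size and power rests on equal arms: "84 autistic children for RUBIES + HELM and RUBIES only vs. 42 children in educator psychoeducation" for Aim 1, and 42 against 42 educators in 28 schools for Aim 2.

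Aim 1 analyses: the school level holds a random intercept and the treatment indicator. Covariates are picked from youth and educator characteristics when the difference between arms reaches an effect size of 0.2 in absolute value. Aim 2 analyses has the same school-level content and refers back to the same covariate rule. Neither section lists school size, possible dyads or cohort.

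**The concern.** Two features of the design pull against each other. Fourteen schools cannot be split equally among three arms, and cutting them into four cells leaves groups too small for each cell to hold all arms evenly. If each cell is handled separately, the remainders add up over the cohorts and the arm totals drift from 14. Stratification then yields less balance on school size and possible dyads than intended.

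The analysis as described does not make up for this. The factors that the trial randomizes by, and cohort, are school-level variables, and the covariate rule looks only at child and educator variables. Whatever imbalance remains on them goes unadjusted. If they predict the outcome, the variance they explain stays in the error term. At stake are some precision in both primary comparisons and protection against an unlucky draw with few schools per arm.

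**Working it through.** **Inputs.** 42 schools, three cohorts of about 14, 1:1:1 within cohort, two median splits (Study design; Randomization). SD 6.2, difference 3.8 on the ABC-I, 5% type I error (two-sided assumed), 10% inflation for clustering, 20% attrition, three dyads per school (Sample size and power).

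**The plan's own figures.** 42/3 = 14 schools per arm; 28 × 3 = 84 and 14 × 3 = 42 children. Two-means formula with ratio 2: controls = 1.5 × (1.960 + 0.842)² × 6.2²/3.8² = 31.3. Inflated by 1.1 and divided by 0.8, the total is 129.3; multiplied by 1.1 and 1.2, it is 124.1. The stated 126 lies between. Power at 84 against 42 is 0.790.

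**Cells.** 2 × 2 cells in three cohorts give 12 cells, and 42/12 = 3.5 schools each.

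**Arm totals.** Simulation, 15,000 runs per scheme, cohorts of exactly 14, no ties at the medians. Block use is an assumption. Ranges cover near-equal cells and independent factors.

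| Scheme | Exactly 14/14/14 | Every arm within 2 schools of 14 |
|---|---|---|
| Blocks of 3, restarted per cohort and cell | 11% to 12.5% | 89% to 95% |
| Blocks of 6, restarted | about 4% | 54% to 57% |
| Blocks of 3, continued across cohorts | 39% to 46% | 100% |
| Blocks of 6, continued | 16% to 17% | 98% |
| Cohort allocated jointly, 5/5/4 rotated | 100% | 100% |

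Misses are thus mostly one or two schools. The exception is restarted blocks of 6, where some arm is off by three or more in 43% to 46% of runs.

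**Power.** Aim 1 by number of control schools (1.1 inflation): 12 gives 0.755, 13 gives 0.774, 14 gives 0.790, 15 gives 0.803, 16 gives 0.813. From a nominal 80%, the variance ratios are (1/(n₁+n₂) + 1/n₃)/(1/28 + 1/14) for Aim 1 and (1/n₁ + 1/n₂)/(2/14) for Aim 2. For example, 12 control schools give (1/30 + 1/12)/(1/28 + 1/14) = 1.089, so power is Φ(2.802/√1.089 − 1.960) = 77%. With restarted blocks, mean power for Aims 1 and 2 is 79.8% and 79.7% (blocks of 3) or 79.4% and 79.1% (blocks of 6). In the worst 5% of draws it is about 77% or 74% to 75% in each aim taken separately.

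**Balance.** The measure is the SD of the RUBIES-minus-control difference in mean school size or possible dyads, in SD units. Without stratification it is √(1/28 + 1/14) = 0.33. With restarted blocks in cells it is about 0.22 to 0.27. With a constrained draw per cohort it is about 0.15, depending on how tight the acceptance rule is.

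**Feasibility.** For every cell layout of a 14-school cohort, from 0/7/7/0 to 7/0/0/7, a 5/5/4 split with each cell balanced to within one school exists. Rotating the short arm gives 5 + 5 + 4 = 14 per arm.

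**Cost of adjustment.** Size (1), possible dyads (1) and cohort (2) use four school-level parameters: 42 − 2 = 40 falls to 36 in Aim 1, and 28 − 2 = 26 falls to 22 in Aim 2.

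**The case against.** The strongest reply is that the article never mentions blocks. A journal article may leave the allocation method to a fuller protocol, and a median split requires the cohort's schools to be known first, so joint allocation of a cohort fits the text. This stands. A reader might infer that incomplete blocks are part of the plan, and the documents do not support that. The frequencies above are conditional on an assumed method.

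Three other tempting readings also fail.

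- **Heavy ties in the dyad split.** The article says "We anticipate recruiting at least two autistic children per school (range 2–5 children per school", but that concerns recruited children. The stratification factor is possible dyads at screening. It has a floor of two from the school inclusion criteria and no stated ceiling.
- **Power lost in both aims together.** Too few control schools hurts Aim 1 but leaves more schools for Aim 2, and the reverse. In simulation with restarted blocks the two powers correlate at −0.95 (blocks of 3) or −0.88 (blocks of 6), and both fall below 79% in 0% or 0.5% of trials. Extra control schools raise Aim 1 power.
- **Allocation alone decides the 84 against 42 split.** That split also depends on dyads per school, where the article says only "We expect 3 child-educator dyads per school to consent and enroll in the study". With exactly 14 control schools and an assumed 2/3/4/5 distribution (probabilities 0.4/0.3/0.2/0.1), exactly 42 control children occur in 11% of runs.

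Stratification also does some good: an SD of 0.22 to 0.27 is better than 0.33.

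The reply does not reach the covariate rule, which the article states itself and which leaves out the factors used in randomization.

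**Conclusion.** The point holds as a modest, cheaply remedied weakness. Two parts rest directly on the text: about 3.5 schools per cell for three arms, and primary models whose described content omits the stratification factors and cohort. The frequency of missing 14 per arm (roughly 88% to 96% of trials with restarted blocks, 54% to 84% with continued blocks) depends on blocks being used within cells, on cohorts of exactly 14 and on untied medians. Average power loss is under one point in each aim. The worst 5% of draws cost about 3 to 6 points in one aim or the other. The clearer gain from a change is in balance, where the SD of the imbalance falls from about 0.22 to 0.27 to about 0.15. None of this makes the trial invalid or its sample size wrong.

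**What to change.** 1. In the Aim 1 and Aim 2 models, prespecify school size, number of possible dyads and cohort as covariates whatever imbalance is observed. In Aim 1, let them enter the growth parameters as well as the intercept, since the comparison is of change. Keep size and dyads continuous.

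2. Allocate each cohort's schools in one step by constrained randomization. Fix near-equal arm counts, for example 5/5/4 with the short arm rotated, adapted to the cohort's actual size because the article says only approximately 14. Draw at random from the allocations that balance school size and possible dyads, and confirm that enough allocations remain acceptable. If the full protocol already specifies joint allocation, one sentence in the Randomization section settles this part.

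The cost is a short program by the biostatistician and four school-level degrees of freedom per model. The Discussion states that no participants had been enrolled as of February 2026. The change secures 14 schools per arm only if the cohorts total 42 as planned, and it does not guarantee the number of children per arm.

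### After schools are randomized, the educator chooses the child, makes the first approach and gives the baseline score, so the Aim 1 change contrast is open to differential selection and baseline rating

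*Protocol article*

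**What the plan says.** **Timing.** The Randomization section states that "Study enrollment, randomization, and engagement for all schools begins in the Spring prior to Year 1". The Study design section lists a first assessment in the "Spring semester prior to the year of school and student enrollment (implementation baseline; arms 1–2") and a second in the "Fall semester Year 1 (clinical baseline; arms 1–3"). Students are therefore enrolled in the school year after randomization.

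**Choice, approach and consent.** Under Autistic children, "Enrolled educators will identify one autistic child with whom they currently work for potential enrollment in the trial". The first contact is also the educator's: "Educators will share information about the study with the child’s caregiver/legal guardian". Research staff then explain the study and "will obtain electronic parent/guardian consent".

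**Eligibility and baseline.** Entry requires SESBI-R ≥ 101 and/or EDI ≥ 8, "at baseline as rated by the educator after the dyad consents". The educator-reported SESBI-R is the primary clinical outcome (Clinical outcomes; Table 1). Aim 1 analyses tests its change from baseline to Week 24, arms 1 and 2 against arm 3. An educator with no eligible child is excluded.

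**Arm-specific activity before the Fall.** Table 1 limits the Spring RUBIES leadership and climate scales to the two RUBIES arms. Implementation outcomes describes an educator questionnaire and interview about RUBIES strategies at the implementation baseline. HELM leaders are trained in the summer before Year 1.

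**Masking.** It is stated for the independent evaluators only.

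**Screening before allocation.** Schools must identify at least two autistic children with externalizing behavior before enrollment (Participants), and the number of possible dyads at screening is a randomization stratum.

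**The concern.** Randomizing schools makes the schools comparable. It does not by itself make the children comparable if they are chosen after allocation by someone who knows the arm. Here one person chooses the child, supplies the score that decides entry, sets the baseline and later rates the endpoint.

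An educator who expects weekly coaching on behavior may nominate a more difficult child, or rate the same child higher, than an educator who expects a self-paced webinar. Either could raise the baseline in arms 1 and 2 relative to arm 3. Part of that rise may disappear by Week 24 without any treatment effect and be read as a RUBIES benefit. The direction is not certain, but a bias of this kind does not shrink as the sample grows.

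**Working it through.** **1. Is the order of events in the text?** Yes. Randomization is in the Spring; child selection and clinical baseline belong to the following school year. The educator chooses among children currently served, so the Fall caseload governs.

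**2. Is the arm known to the educator?** This is not stated. Three facts point to it: no educator masking is described, the Spring RUBIES assessments run in arms 1 and 2 only, and those assessments include an educator interview on RUBIES strategies. The inference is strong for arms 1 and 2 and weaker for arm 3.

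**3. Does screening fix the child?** No. The two-child requirement and the dyad count describe the school. Nothing says that the children counted are the ones enrolled.

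**4. The plan's own Aim 1 figure.** Inputs from Sample size and power: difference 3.8, SD 6.2, 84 vs 42 children, 20% attrition, 10% inflation, alpha 0.05 (taken as two-sided).
- Effective control n = 42 × 0.8 / 1.1 = 30.5; RUBIES n = 61.1.
- SE = 6.2 × √(1/30.5 + 1/61.1) = 1.37.
- Power = Φ(3.8/1.37 − 1.96) = 79.0%, against the stated 80%.

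The figure reproduces. It allows for no selection or rating bias.

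**5. How much of a baseline shift reaches the change contrast?** Let δ be the between-arm baseline shift in SD units and r the baseline to Week 24 correlation, with no true treatment effect. The documents give no δ, so 0.1–0.5 SD is assumed.
- *Rating inflated at baseline only:* spurious change = δ.
- *Selection on a noisy score:* the follow-up shift is rδ, so spurious change = δ(1 − r).
- *Choice of a stably more severe child:* baseline and follow-up shift together, so spurious change may be near 0.

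| δ (assumed) | Rating inflation | Selection, r = 0.3 | Selection, r = 0.87 |
|---|---|---|---|
| 0.1 | 0.10 | 0.07 | 0.01 |
| 0.3 | 0.30 | 0.21 | 0.04 |
| 0.5 | 0.50 | 0.35 | 0.07 |

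The value r = 0.3 is the plan's assumption, which it calls conservative. The value 0.87 is the SESBI-R Intensity test–retest correlation under Clinical outcomes. It is not a 24-week correlation and serves only as an upper bound on r.

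**6. Effect on the test, worst mechanism.** With full pass-through and the SE from step 4, the type I error is Φ(b/SE − 1.96) + Φ(−b/SE − 1.96), where b = 6.2δ. For δ = 0.1, 0.2 and 0.3 (b = 0.62, 1.24 and 1.86 points) it is about 7%, 15% and 27% instead of 5%. With a design effect of 1 + (3 − 1) × 0.10 = 1.2 it is 7%, 14% and 25%. The SD of 6.2 belongs to the ABC-I, on which the power calculation was done, so this is an illustration and not a forecast for the SESBI-R.

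**The case against.** The strongest reply has four parts.

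- **Disclosure of the arm is not described.** The article is condensed, the timeline figure is not shown, and the full protocol may say when educators learn their arm. This stands: arm knowledge is an inference. Who chooses the child, who rates, and that both come after randomization do not depend on it.
- **Safeguards exist.** Candidate children are identified before enrollment, possible dyads are counted for stratification, all arms share one entry threshold, and research staff take consent. These narrow the room for bias. They do not fix the enrolled child or mask the baseline score, and staff can seek consent only from caregivers whom the educator has approached. The rule of adding covariates at an effect size of 0.2 or more acts on measured characteristics only. The masked CGI-I is only partly independent, because it draws on the educator's narrative and ratings.
- **The magnitude is soft.** This stands. No shift is documented, the result depends on the mechanism and on r, and a rating habit that persists to Week 24 would largely cancel out of the change score.
- **Full masking conflicts with the Spring assessments.** This also stands. A reader might infer that only arm 1 leaders need to know the arm early, but arm 2 also completes the RUBIES-specific Spring assessments.

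A reader might also infer that educators obtain consent. The text assigns that to research staff. Nor is the intent-to-treat comparison broken: enrolled dyads can still be analyzed as assigned. What is at risk is the comparability of the children who enter.

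**Conclusion.** The concern holds as a risk created by the stated procedure. Child selection, first approach, eligibility rating and primary-outcome baseline all rest with an educator who is not stated to be masked, after the school has been randomized. The Aim 1 contrast is therefore open to differential selection and differential baseline rating.

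The size is unknown. Under an assumed shift of 0.1–0.5 SD, it runs from near zero (a stably more severe child), through 0.01–0.07 SD (selection, r = 0.87) and 0.07–0.35 SD (selection, r = 0.3), to 0.1–0.5 SD (rating inflation at baseline only). It is tempting to set one of these against the planned d = 0.62 and quote a fixed share of the effect. The documents do not support that: the shift is assumed, and the 0.62 is for the ABC-I while the primary outcome is the SESBI-R.

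The conclusion rests on the sequence in the text and on the inference that educators know their arm. No analysis can fully repair the problem afterwards. The Discussion reports no participants enrolled as of February 2026, so the procedure could still be changed at that date.

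**What to change.** 1. **Take the choice of child from the educator.** At the pre-randomization dyad screening, or from Fall caseloads when classes change, build each educator's roster from objective criteria: autism documented in the IEP, grades K–5, ages 5–12, and currently on that educator's caseload. The study team draws the index child and a reserve order at random.
2. **Order of disclosure.** Where the school calendar allows, obtain caregiver consent and the baseline SESBI-R, EDI and ABC-I before educators are told their arm. The Spring assessments in arms 1 and 2 may prevent this in part; state any remaining unmasked baseline rating as a limitation.
3. **Reporting.** Give by arm the numbers of children listed, approached, consented and eligible, and of educators excluded for having no eligible child.

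The cost is some added screening coordination and repeat draws when class lists change. The random draw removes discretion over which child enters; it does not mask the baseline rating, which is why the second and third steps are also needed.
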